**Figure 2 F2:**
[figure not shown]
Overview of Intervention Implementation Design.

During the 6-month pre-implementation period, our onsite research coordinators recruit a no-intervention (control/comparison) group of study participants and conduct risk factor screening on recruited patients using paper-based version of the same screening tools as those in Connect Care that will be used during SBIR implementation. These patients do not receive risk factor screening by clinical team members and are not offered brief intervention and referrals. The 15-month SBIR implementation serves as the intervention period of the study during which patients are recruited to participate in the intervention group. Note that all patients served by the participating clinics/units during the intervention period are *eligible* to receive the SBIR intervention, regardless of whether or not they agree to participate in the research study. Over the course of the 15 months intervention period, as the SBIR practice is increasingly embedded into routine care, we expect a growing proportion of the patients served by the participating clinical teams will receive SBIR. Enrolled research participants are followed up over the course of 12 months (1, only for intervention group, 6, and 12 months) for collection of behaviour change and health services utilization data. During the monitoring of participant recruitment, any control participants who had subsequent visits to intervention sites and received the intervention at that time were excluded from the study.

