**Pre-implementation Phase (6 Months Control Period)**				

Baseline, for comparison of SBIR (Screening Brief Intervention, and Referral) effectiveness	Tobacco consumption, alcohol intake, and physical activity levels	Proportion of patients with tobacco consumption, alcohol misuse, and insufficient physical activity levels	Primary data collection from comparison patient group	Paper-based self-administered questionnaire

Pre-implementation (baseline) delivery of SBIR elements by clinical team members.	Providers’ baseline delivery of SBIR elements to patients	Proportion of patients being screened, advised, and referred for each risk factor	Connect Care documentation (electronic health records)	Connect Care data extraction, monthly time points for six months

Baseline	SBIR implementation readiness	Leadership engagement/support, resources for SBIR, providers’ motivation	Primary data collection from providers and organizational leaders	Self-administered questionnaire, interview, and observation

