Patient follow ups: Effectiveness of SBIR intervention	Patients’ behavior change status for both control and intervention patient groups	Intention to change behavior, awareness about the problem, commitment to action, uptake to referral programs, active modification of behavior (such as quit attempt, reduce/quit tobacco use, reduce/stop alcohol intake, and initiate/increase physical activity). Covariates for effectiveness outcomes: Sociodemographic/socioeconomic (such as age, sex, marital status, ethnicity, education, employment, income, rurality, immigration-related factors) and overall physical and mental health status.	Primary data collection from patients.	Follow-up telephone interview at six months of index hospitalization discharge/visit. Data collection tool will include the questionnaires guided by the Prochaska model of change process and the risk factor screening questions included in the Connect Care

Healthcare resource use	Hospital readmissions and emergency visits for both control and intervention patient groups	Hospital readmissions and emergency visits during the year after index hospitalization discharge /visit. Reasons/diagnosis for readmissions and emergency visits, and family physician/primary care visits within 1-year of discharge/visit and diagnoses/comorbidities at the time of recruitment to 1-year of index hospitalization discharge/visit.	Administrative health databases: Discharge Abstract Database, National Ambulatory Care Reporting System, and physician claim databases	Data from multiple databases will be accessed through Data and Analytics. and will be linked with the follow-up interviews using the personal health numbers.

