## Research plans for evaluation of intervention effectiveness outcomes

*Study design and participants:* We use a quasi-experimental study design (pre-post with a comparison group). The intervention group are patients from participating units during the SBIR implementation period who screen at increased risk on any of the three risk factors and received brief intervention and referral support. The comparison group are patients from the same units, during a 6-month pre-implementation period, identified as having increased risk on any of the three risk factors, but who do not receive the SBIR intervention.

Study inclusion criteria for the target patient population to be enrolled in the effectiveness study include: Adult patients (>18 years) who are residents of Alberta, have the ability to engage in the SBIR process and data collection, and are attending the participating sites during the study period. Research assistants enroll the eligible patients in the study after they provide informed consent. The patients with severe disease conditions (i.e., unconsciousness and end-stage care) or those with mental or cognitive incapacity are excluded.

*Outcome definition and measurement for both groups:* Key outcomes are patient behaviour change in relation to the modifiable risk factors and health care utilizations in the year after recruitment to the study. Measurement of patient’s behaviour changes involves: questions on patients’ intention to change behaviour, their uptake of referral services (for those who received referrals), and changes in risk level as measured using the same risk factor screening tools used during the SBIR intervention. We also ask patients about tobacco use reduction, tobacco quit attempts, seven- and 30-day tobacco abstinence. The data are being collected via telephone interviews at 6 months follow-up after the index clinic visit, or discharge from a hospital stay, during which the patient was recruited into the study. A sample of participating patients are also called at 1 month after their hospital/clinic visit to ask them about their experience of the SBIR intervention.

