Health care utilization measures include hospital readmissions and emergency visits within one year of the index discharge/visits. These outcomes are of particular importance to facilitate outcome comparisons with other studies as well as because they are important to provide cost-effectiveness assessments to support intervention spread/scale decisions by health system administrators. The health care utilization data will be obtained from linked administrative health databases accessed through the Department of Data and Analytics, the custodian of these routinely collected healthcare data (Table 1).

Data on potential confounding variables including sociodemographic and socioeconomic status for both groups are collected during the 6 months patient follow-up interviews. Diagnosis and comorbidity related variables will be obtained from the administrative health databases. A detailed data collection plan is shown in data collection matrix (Table 1).

*Sample size:* SBIR intervention can increase smoking quit rate at 6-months by 11% [40], reduce alcohol misuse rate at 5-months by 19% [41], and increase patients’ average daily physical activity level by 22% [42]. Based on sample size estimation in relation to tobacco use (with effect size of 11%), we will need a maximum of 1,000 patients in each group (a total sample of 2,000 for controlled and intervention groups) to detect the smallest difference, among all outcomes, between the groups (with a study power of 80% and alpha of 0.05). This is the maximum number needed since tobacco is the least prevalent condition and it will also have the smallest proportion of change in behaviour after intervention, among the three risk factors. We will recruit a total sample of 4,000 (2,000 sample for controlled group and 2,000 for intervention group) to account for the anticipated 50% loss to follow up or nonresponse rate. The expected dropout rate is determined based on our previous paper-based SBIR pilot study [22].

*Analysis:* We will use log-binomial regression models to estimate risk difference and relative risk (for health behaviour change outcomes), and Cox proportional competing risk regression models to estimate hazard rate difference and hazard ratio (for health care use outcomes), to compare outcomes between the two groups adjusting for confounders, such as reasons or diagnosis for visits/admissions, comorbidity, and socioeconomic status.

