Self-administered questionnaires are used to assess risk factors in the control group. These same questionnaires are integrated into the Connect Care system to support provider-led screening within routine clinical workflows, which are used for risk factor screening in the intervention group. Social desirability bias can be present when patients respond to questions about their health-related behaviours. However, we have no reason to expect the bias in responses to the risk factor questions will be different between the control and the intervention groups. Additionally, the follow ups at 6 months and 12 months to measure behavior change and healthcare use outcomes, respectively, may underestimate the intervention’s ultimate effects, as the outcomes may take a longer period to manifest. However, existing literature has demonstrated measurable changes within these timeframes [40,41,42,55], and demonstrating near-term impact was a key criterion for the grant funding mechanism supporting this project.

We acknowledge that effective prevention care ideally addresses the full prevention continuum; however, this was beyond the scope of the current project, which focused on establishing improved processes for delivering preventionrelated care within hospital settings. Within our intervention approach, patients who expressed interest in behavior change were encouraged and supported to access relevant communitybased services and supports. Because direct referral pathways within the Alberta health system were available only for certain behavior change needs (specifically smoking cessation and highrisk alcohol consumption), some referrals were necessarily informational and patientdirected. Hospital-anchored prevention pathways are simply one of many on-ramps that need to be made available to patients/people to support the promotion of health and the reduction of illness and its related health system costs. Ultimately, health promotion through primary care and through intersectoral partnerships to create supportive health environments in community will be vital to improving population health and reducing avoidable hospitalization.

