## Expected Results and Applicability

Thus far 4 inpatient units and 4 ambulatory clinics in Calgary and Edmonton cities in Alberta have participated in this project. Among those, 1 inpatient unit and 4 ambulatory clinics have completed the 6 months control period and started the implementation of SBIR, and remaining units/clinics are in the 6 months control phase. We have recruited a total of 2015 patients as control research participants (i.e., medium or high-risk level on any of the three risk factors). Of those, 1000 have completed 6 months follow-up calls. A total of 447 patients have received SBIR support from the participating units/clinics, with 175 patients being intervention research participants (i.e., consented for follow up survey). Among those intervention research participants, 48 have completed 1 month follow up survey calls, 75 have completed 6 months follow up calls, and 23 have participated in in-depth qualitative interviews. Approximately 50% of patients are responding to follow-up efforts.

The research participants recruitment and data collection activities are undergoing and key learnings to date are as follows.

High screening uptake: Providers are consistently screening and documenting for the risk factors.Low brief intervention rates: Offering brief advice or engaging patients in conversations about behavior change remains relatively low.Low documentation of brief intervention: When brief interventions are provided, they are often not documented in the Connect Care system.Referral gaps: Referral pathways—particularly for physical activity and alcohol use—are unclear, and referral functionalities for these risk factors are not currently integrated into the Connect Care system.Facilitators of implementation: Implementation is supported by clinical champions, embedded project staff at implementation sites, and ongoing rapid assessment and feedback.Participant eligibility challenges: Many patients are ineligible for the intervention or study participation due to critical health conditions particularly in some high acute care settings. This indicates that careful consideration of the setting and patient acute is important when deciding whether to implement SBIR.Improved recruitment: Using both in-person and phone-call recruitment strategies has led to an increase in participant numbers.

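### Baseline risk level is measured in both groups but is not among the covariates or confounder sources the protocol names, so a different risk mix between periods could bias the behaviour-change estimates in either direction

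*Protocol article*

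**What the plan says.** The effectiveness section of the protocol article describes the design as follows: "We use a quasi-experimental study design (pre-post with a comparison group"). Controls come from a 6-month pre-implementation period and intervention patients from the later implementation period in the same units.

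Both groups have an individual baseline. Under the design heading in Methods, the research coordinators "conduct risk factor screening on recruited patients using paper-based version of the same screening tools as those in Connect Care". The Disadvantage section says the same questionnaires sit in Connect Care, "which are used for risk factor screening in the intervention group". Table 1 labels the control screen "Baseline, for comparison of SBIR (Screening Brief Intervention, and Referral) effectiveness".

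Entry covers a range of starting risk. Expected Results and Applicability reports: "We have recruited a total of 2015 patients as control research participants (i.e., medium or high-risk level on any of the three risk factors"). Intervention patients must screen at increased risk on any factor and must also have received brief intervention and referral support.

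The behaviour outcomes include "changes in risk level as measured using the same risk factor screening tools used during the SBIR intervention", together with intention to change, uptake of referral services, tobacco reduction, quit attempts and abstinence at 6 months.

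The adjustment is described in three places:
- The Analysis paragraph says the models are used "to compare outcomes between the two groups adjusting for confounders, such as reasons or diagnosis for visits/admissions, comorbidity, and socioeconomic status".
- Table 1 gives "Covariates for effectiveness outcomes: Sociodemographic/socioeconomic (such as age, sex, marital status, ethnicity, education, employment, income, rurality, immigration-related factors) and overall physical and mental health status".
- The paragraph on confounders takes sociodemographic and socioeconomic data from the 6-month interview, and diagnosis and comorbidity from administrative databases.

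None of the three mentions the baseline screening result.

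**The concern.** How a patient starts on a behaviour is likely to be a strong predictor of where that patient stands 6 months later. A patient at high risk has further to fall and more regression to the mean than one at medium risk, while a heavier user may find it harder to quit. Either way, the outcome depends on the starting level.

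Randomisation would balance that level, but this design has none. The entry rules also differ between the groups. Controls need only be at increased risk. Intervention patients pass a further filter, receipt of brief intervention and referral, and the article gives reasons to think that filter is selective:
- Providers judge suitability and patients may decline.
- Brief advice is reported as relatively infrequent.
- Direct referral existed only for smoking cessation and high-risk alcohol use.

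The filter could shift both the level of risk and the type of risk factor in one group only. Diagnosis, comorbidity and socioeconomic status are weak stand-ins for that. At stake are the risk ratio and risk difference for behaviour change, which are the main effectiveness results.

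**Working it through.** **Plan's own figure.** The article needs 1,000 evaluable patients per group and expects 50% loss: 1,000 / (1 − 0.50) = 2,000 recruited per group, as stated. The 1,000 itself cannot be re-derived, because no control quit rate is given. It is used below only as the number analysed.

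**Is baseline named anywhere in the adjustment?**

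| Place | What is named | Baseline risk level or factors present? |
|---|---|---|
| Analysis paragraph | visit reason or diagnosis, comorbidity, socioeconomic status (open list) | no |
| Table 1, effectiveness row | sociodemographic and socioeconomic items, physical and mental health | no |
| Confounder data sources | 6-month interview, administrative databases | no |

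**Size if it is left out.** The inputs below are assumptions, since the article gives neither the medium/high split nor improvement by level:
- no true SBIR effect;
- probability of improving p_H if high risk and p_M if medium risk at baseline, the same in both groups;
- share at high risk h_C in controls and h_I in the intervention group;
- n analysed per group.

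Formulas:
- expected proportion improving: p = p_M(1 − h) + p_H·h
- spurious difference: (p_H − p_M)(h_I − h_C)
- SE = √[p_C(1 − p_C)/n + p_I(1 − p_I)/n], and shift z = (p_I − p_C)/SE
- two-sided rejection rate: Φ(|z| − 1.96) + Φ(−|z| − 1.96)

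Worked case, p_H = 0.30, p_M = 0.15, h_C = 0.50, h_I = 0.60, n = 1,000:
- p_C = 0.15 × 0.5 + 0.30 × 0.5 = 0.225
- p_I = 0.15 × 0.4 + 0.30 × 0.6 = 0.240
- difference 0.015; SE = 0.0189; z = 0.79; rejection rate 12.5% instead of 5%

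Range at 1,000 per group, h_C = 50%:

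| p_H / p_M | h_I = 60% | h_I = 70% |
|---|---|---|
| 0.25 / 0.15 | +1.0 point, 8.6% | +2.0 points, 19.6% |
| 0.30 / 0.15 | +1.5 points, 12.5% | +3.0 points, 34.9% |
| 0.40 / 0.20 | +2.0 points, 16.2% | +4.0 points, 48.4% |

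A 5-point shift in mix gives only 6% to 8%.

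**Smaller analysis sets.** Patients qualify on any one of three factors, so the number at risk on a given factor is below the group total. For 0.30/0.15, with assumed per-factor numbers:

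| n per group | 50% vs 60% | 50% vs 70% |
|---|---|---|
| 300 | 7.2% | 13.8% |
| 200 | 6.5% | 10.8% |

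The false-positive rate falls because the SE grows. The spurious difference (1.5 or 3.0 points) does not change.

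**Direction.** If medium-risk patients improve more, the sign reverses. With p_M = 0.30, p_H = 0.10, h_C = 40%, h_I = 50% and n = 1,000, p_C = 0.22 and p_I = 0.20. The difference is −2.0 points (risk ratio 0.91), which would hide a benefit of that size. Reversing the gradient (p_M = 0.10, p_H = 0.30) gives +2.0 points (risk ratio 1.11).

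**With baseline level in the model.** Within each level the expected difference is zero by construction, so the spurious difference disappears. That holds because starting level is the only confounder in the example and is measured without error.

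**The case against.** The strongest reply is that the Analysis list is introduced as examples. A journal article need not print the full covariate set, and an analysis plan not shown may well contain baseline risk. That stands: a reader might infer that the trial has decided to leave baseline out, and the document does not support that reading. What remains is narrower. The article names covariates in two places and their sources in a third, and passes over the one variable that Table 1 itself labels as the baseline for the comparison.

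A second reply is that change in risk level already uses the paired baseline. It does, for that outcome. But a change score still depends on the starting level, and intention, quit attempts and abstinence are follow-up answers that are not conditioned on starting use. Change score versus baseline adjustment in non-randomised groups is a debated choice, so this is not a plain error.

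Third, the groups are not wholly unbalanced: they share units and are restricted to increased-risk patients. That is partial balance only, since the range within that restriction stays open.

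Finally, a reader might infer that a false SBIR benefit will be reported. The document does not show this. Bias needs both a differing mix and an outcome gradient by level, neither is given, and the sign could go either way. The calculation is also crude, whereas the plan adjusts for other covariates that may absorb part of the difference.

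**Conclusion.** The point holds in a conditional form. Baseline risk level and the factors present are collected in both groups but are absent from the covariates and confounder sources the article names. If the named adjustment is all that is done, a difference in risk mix between periods can bias the behaviour-change estimates towards or away from an SBIR effect.

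Under the stated assumptions with a 10-point shift in mix, the spurious difference is 1 to 2 points. The false-positive rate is 9% to 16% with 1,000 per group and about 7% with 300 per group (0.30/0.15 case). A 20-point shift is more serious, and a 5-point shift matters little. These are illustrations, not estimates for this trial. The change is worth making because it costs almost nothing and the variable is an obvious candidate in a non-randomised comparison.

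**What to change.** For each risk factor, define the analysis set as patients at risk on that factor at baseline. In the log-binomial models for that factor, include the baseline screening level on it and the number of factors at risk, alongside the covariates already named. State this in the Analysis paragraph and in the Table 1 covariate entry, and add the recruitment screen to the listed confounder sources.

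No new data collection is needed, and the article says analysis waits for complete data, so this is a change of wording. The costs are slightly more complex models and smaller per-factor sets, whose sizes should be reported.

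The change reduces confounding by starting risk. It does not remove bias from other unmeasured differences between the periods, or from the different screening modes (self-administered in controls, provider-led in the intervention group), which could make the recorded baseline levels less comparable.

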## Methods

### The design and key features of implementation and evaluation

We employ implementation-effectiveness hybrid study using mixed-methods [26]. This includes quasi-experimental design for quantitative assessment of SBIR implementation (adoption/coverage of intervention) and effectiveness (patient behaviour change and health service use) outcomes. We use both quantitative and qualitative methods to evaluate the implementation processes and providers’ experience of integrating SBIR into their workflows and patients’ experience of the SBIR intervention and of health behaviour change. Each participating site participates in a 6-month pre-implementation period, followed by 15-month SBIR implementation research period. Patients are followed up at 1, 6, and 12 months after they receive the SBIR intervention (Figure 2). Clinical sites that had used Connect Care for at least 6 months prior to recruitment into this project, and where the team identified health promotion and disease prevention as a priority, and expressed interest in participating in the study were engaged to participate.

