### Research plans for evaluating implementation outcomes and process

*Study design and participants:* We use a quasi-experimental interrupted time-series design, covering a 6-month pre-implementation period and the last 12 months of the 15-month SBIR implementation period. The first three months of the implementation period are not used in analysis because we expect the quality of the SBIR intervention will mature over the first few months during which the clinical team learn to apply the practice.

*Definition and measurement of implementation outcomes*: Intervention reach (number) and patient population coverage (proportion) will be measured for each component of the SBIR intervention. Thus, the number of patients i) screened; ii) advised; and iii) referred in relation to each risk factor will be extracted each month from the Connect Care data. The denominator for the coverage (proportion) measures will be based on the total number of patients seen by a participating unit in the same month.

*Analysis:* For each outcome, we will calculate monthly summaries, aggregated across participating units. A Poisson regression model will be used to estimate the difference between the post-intervention observed rate and the “spontaneous” rate that would have occurred had SBIR been not implemented. The analysis will account for seasonality by decomposing the data in trend, seasonal, and random components, and then removing the seasonal component.

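### The effectiveness models compare an earlier control period with a later intervention period but name no unit, season or calendar-time term, so unit mix and season can be read as an SBIR effect.

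*Protocol article*

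**What the plan says.** The design section of the protocol article states: "Each participating site participates in a 6-month pre-implementation period, followed by 15-month SBIR implementation research period". For the effectiveness outcomes, "The comparison group are patients from the same units, during a 6-month pre-implementation period"; the intervention group comes from those units once SBIR has begun.

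The effectiveness Analysis paragraph names log-binomial models for behaviour change and Cox competing-risk models for health care use. Both compare the two groups "adjusting for confounders, such as reasons or diagnosis for visits/admissions, comorbidity, and socioeconomic status". Table 1 gives a second list: "Covariates for effectiveness outcomes: Sociodemographic/socioeconomic (such as age, sex, marital status, ethnicity, education, employment, income, rurality, immigration-related factors", plus overall physical and mental health. Both lists are at patient level.

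For the implementation outcomes, the article does deal with time: "The analysis will account for seasonality by decomposing the data in trend, seasonal, and random components". Nothing comparable appears for the effectiveness outcomes, and the Disadvantage section does not discuss confounding by time or unit.

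Expected Results and Applicability counts 4 inpatient units and 4 ambulatory clinics. Of these, "1 inpatient unit and 4 ambulatory clinics have completed the 6 months control period and started the implementation of SBIR", and the "remaining units/clinics are in the 6 months control phase".

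**The concern.** In a before-and-after comparison, the main rival explanation for a difference is whatever else differs between the periods. Two such differences are built into this design.

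- **Season.** Within one unit, a 6-month control intake covers half a year, while a 15-month intervention intake covers a full year plus three months. The two cannot have the same seasonal make-up. Behaviour is measured again six months after the index visit, so a control intake in one half-year is followed up in the opposite half. Physical activity is the outcome most plausibly affected.
- **Unit mix.** Inpatients and ambulatory patients are likely to differ in readmission risk and readiness to change. Drawing controls from the same units removes this only if each unit supplies the same share of both groups.

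The estimates also feed the cost-avoidance analysis and decisions on spreading SBIR to other hospitals.

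**Working it through.** **1. Interim unit split (from the article).** Inpatient units still in the control phase: 4 − 1 = 3. Ambulatory clinics still in control: 4 − 4 = 0. At that date there were 2,015 control participants, drawn from all eight units, and 175 intervention participants, who could come only from the four clinics and one inpatient unit. Counts per unit are not reported.

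**2. Unit mix (assumed inputs).** Take one-year admission risks of 35% inpatient and 15% ambulatory, with controls half inpatient.
- Controls: 0.5 × 0.35 + 0.5 × 0.15 = 0.25.
- Intervention group 20% inpatient: 0.2 × 0.35 + 0.8 × 0.15 = 0.19; crude ratio 0.19/0.25 = 0.76 with no effect of SBIR.
- At 35% inpatient: 0.22/0.25 = 0.88. At 10%: 0.17/0.25 = 0.68.

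**3. Season (assumed sine wave of amplitude a; one unit; uniform intake aligned with the season).**
- Mean of a half-cycle: 2a/π = 0.637a.
- Control change over six months: 2 × 0.637a = 1.27a in size.
- Intervention intake: twelve of the fifteen months cancel. The other three (one fifth) average 0.637a with opposite sign, so the change is 2 × 0.637a/5 = 0.25a the other way.
- False difference: 1.53a, about 15 points at a = 10 and about 8 at a = 5.

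**4. Secular trend (assumed drift).** The phase midpoints are month 3 and month 6 + 7.5 = 13.5, a gap of 10.5 months. Bias = annual drift × 10.5/12. For 1, 2, 3 and 5 points a year this is 0.9, 1.75, 2.6 and 4.4 points. Read as absolute points, the planned tobacco effect is 11.

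**5. Combined, by simulation under no effect.** Assumptions: 5 early and 3 late units, lag 6 months, 1,000 responders per arm, drift 3 points a year, seasonal amplitude 3 points, a 10-point difference between unit types, and shares of 70/30 against 30/70.

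| Terms | Estimate (points) | Rejection rate |
|---|---|---|
| None | +5.9 | 89% |
| Unit | +2.4 | 20% |
| Unit and calendar month | +0.3 | 4.5% |

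**6. Clustering (assumed).** With m = 1,000/8 = 125 per unit and phase and cluster autocorrelation 0.8, the design effect is 1 + (m − 1)ρ − 0.8mρ.
- ρ = 0.01: 1 + 1.24 − 1.00 = 1.24; square root 1.11.
- ρ = 0.02: 1 + 2.48 − 2.00 = 1.48; square root 1.22.
- Standard errors that ignore clustering would be 1 − 1/1.11 = 10% to 1 − 1/1.22 = 18% too small.

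**7. What the terms cost.** These are variances of the group contrast relative to no added terms, for 5 early and 3 late units, start lags of 3 to 12 months, and late units contributing 3 to 15 intervention months.
- Unit terms: 0 to 11% more.
- Unit plus one sine/cosine pair: about 2 to 81% more in total.
- Adding a linear trend: about 3.4- to 5.6-fold.
- Full calendar-month effects (step 5; lags 3 to 9 months): about 6.6- to 9-fold. A rank check shows the effect is then estimable at every lag tested from one month up, but not if all units start together.

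**The case against.** The strongest reply is that the adjustment list is open-ended and an article may leave the full covariate list and variance estimator to an analysis plan. That stands in part. A reader might infer that the models adjust for patient characteristics only and treat patients as independent. The article says neither; the supportable statement is that no unit, season or time term is named. The point still holds, because two separate lists omit these terms while the same article specifies trend and season for its other analysis.

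Second, the unit imbalance is an interim snapshot. Late starters necessarily have controls only at first, each site is planned to pass through both phases, and analysis waits for complete data. A reader might infer that the final groups will be this unbalanced; the article does not show it.

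Third, the 0.76 is a crude ratio. Diagnosis or reason for admission is a named adjuster and partly stands in for unit type. In that example, any adjustment that fully separated inpatient from ambulatory patients would return 1.0. The 15-point figure needs a single unit, aligned intake and a large assumed swing; staggered starts would generally dilute it, and the argument is weaker for tobacco and alcohol.

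Fourth, sites were chosen to have no other major initiative under way. This partly guards against co-interventions, but not against season or unequal unit shares.

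**Conclusion.** The point holds as a defect in the stated effectiveness analysis. The contrast is between periods, the named adjusters do not address period or unit, and run as written it can attribute unit mix and season to SBIR. The direction and size of the bias cannot be determined from the article. All magnitudes above rest on assumed risks, shares, swings, drift, start lags and intraclass correlations. The unit-mix ratio and the seasonal figure precede the planned diagnosis adjustment, so they illustrate scale and do not predict it.

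A reader might also infer that the staggered start lets the model remove secular trend cleanly. That goes too far. It requires a trend common to all units, yet at the interim date the late units are all inpatient and four of the five early ones are ambulatory, and start dates are not given. The precision cost is also large. Unit and season terms are a cheap to moderate improvement for the primary models; a trend term is a trade-off better suited to a sensitivity analysis. The primary models would then still carry any secular drift, so it must be stated as a limitation.

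**What to change.** In every effectiveness model:
- include unit as a fixed effect, stratifying the Cox baseline hazard by unit;
- include one sine/cosine pair for month of index visit or discharge;
- include the participant's baseline level of the risk factor;
- use standard errors that allow for clustering by unit, with a small-sample correction suited to eight units.

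Report the contrast within units that contributed to both phases.

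Pre-specify a sensitivity analysis that adds a linear calendar-time term, supported by the staggered starts. State that it assumes one trend for inpatient and ambulatory units and may raise variance roughly 3- to 6-fold. List residual secular trend among the limitations.

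**Cost.** No new data should be needed: the unit is the recruitment site, the index date anchors follow-up, and risk level is screened at entry. Unit terms lose little precision, season terms a modest to moderate amount, and intervals will be less favourable overall, so power should be looked at again. The terms should be fixed before the complete data are analysed, because adding them later would look post hoc.
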